### Statistical considerations

Categorical data are summarized as numbers and percentages, while continuous data are presented as mean values with SDs or as median values with IQRs, as appropriate. Cumulative incidence curves will be generated with the use of the Aalen–Johansen estimator, which accounts for competing events (eg, cardiovascular and noncardiovascular death). For noncompeting events, Kaplan-Meier curves will be used. Since the risk of events is not constant over time, cumulative incidence will be presented instead of incidence rates. For repeated events (eg, appropriate and inappropriate shocks and complications), cumulative hazard rate will be provided using the Nelson-Aalen estimator.

For multivariate analysis, a Cox proportional hazards model will be employed, using the Breslow method to handle tied event times. Time until events is recorded in days to minimize ties. A frailty term will be included to account for variability between trial sites, with center effects embedded as random to capture differences in clinical practices and center experience. For competing events (eg cause-specific deaths), both cause-specific hazard rate and subdistribution hazard rates will be calculated, with the Fine and Gray model used for sensitivity analyses. Prespecified predictors will be 1) patient characteristics (eg, age, sex, body mass index, prevention type [primary vs secondary], underlying heart disease category, left ventricular ejection fraction, prior ICD); 2) procedural/device characteristics (eg, incision technique [2-incision vs 3-incision], generator position [intermuscular vs subcutaneous], anesthesia type, defibrillation testing [performed vs not], device generation/type, SmartPass filter status); and 3) calendar time/center factors (eg, implant year/era, implanting center volume), when available.

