For the analysis of appropriate and inappropriate shocks, the Anderson and Gill model will be applied, incorporating a robust sandwich variance estimator to correct for correlations between recurrent events within the same subject. Shocks occurring within the same episode (cluster) will be counted as a single shock. As a sensitivity analysis, a negative binomial model will be used to account for all shock episodes. For complications and complications requiring intervention, the Wei, Lin and Weissfeld model will be employed to account for repeated events of different nature, identifying factors associated with increased or reduced risks. The center effect will be examined as a fixed effect, categorized by centers with S-ICD implantation volumes greater or <100.

Follow-up will be censored in cases of loss to follow-up, device removal, death, or at the study’s end. The proportional hazards assumption will be assessed using statistical tests and graphical diagnostics based on scaled Schoenfeld residuals. Missing data will be described and handled using multiple imputation strategies. Clinically relevant variables and variables known to be outcome-related from existing literature will be included in the models.

Adjusted subgroup comparisons will be performed using inverse probability weighting based on propensity scores derived from logistic regression models incorporating age, body mass index, indication (primary vs secondary prevention), underlying heart disease, left ventricular ejection fraction, concomitant pacing system, prior ICD, anesthesia type, number of incisions, generator position, generator generation/type, and use of the SmartPass filter. Covariate balance before and after weighting will be evaluated using standardized mean differences, with standardized mean differences <0.10 indicating adequate balance, and will be visualized using Love plots.

To account for potential temporal confounding, outcomes will be analyzed stratified by calendar period and/or device generation, enabling interpretation of event rates in the context of evolving technology and clinical practice.

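### The shock model allows only for correlation within a patient, so tests of centre volume and, less so, of centre-clustered techniques are too liberal if shock rates vary among centres

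*Protocol article*

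**What the plan says.** All statements are in the Protocol article, Statistical considerations.

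- **Multivariate analysis.** "For multivariate analysis, a Cox proportional hazards model will be employed". Centre enters as a random effect: "A frailty term will be included to account for variability between trial sites, with center effects embedded as random". The stated purpose is "to capture differences in clinical practices and center experience".
- **Prespecified predictors.** These include a centre-level variable, under "calendar time/center factors (eg, implant year/era, implanting center volume". They also include procedural choices: "incision technique [2-incision vs 3-incision], generator position [intermuscular vs subcutaneous], anesthesia type, defibrillation testing [performed vs not".
- **Shocks.** The Andersen-Gill model is used, "incorporating a robust sandwich variance estimator to correct for correlations between recurrent events within the same subject". A negative binomial model serves as sensitivity analysis. The Wei, Lin and Weissfeld model is used for complications.
- **Centre in the recurrent-event paragraph.** "The center effect will be examined as a fixed effect, categorized by centers with S-ICD implantation volumes greater or <100". This sentence directly follows the one on the Wei, Lin and Weissfeld model, so it is unclear whether it also covers the shock model.

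That paragraph states no centre frailty and no clustering by centre. Significance is judged at two-sided 0.05 without correction for multiple tests.

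**The concern.** A patient-level sandwich treats patients as independent of each other. A two-class volume term removes only the mean difference between the classes, and differences among centres within a class remain. Volume is constant within a centre, so the information on its effect is limited by the number of centres, above all by the number in the smaller class, and not by the 4,924 patients. Procedural choices share the problem to the extent that they follow the centre.

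The plan itself presumes such centre differences, since it gives them as the reason for the Cox frailty. At stake are the inferences on which centre and procedural factors relate to appropriate and inappropriate shocks. Defibrillation testing and anaesthesia are among the questions that the Discussion says the cohort can address.

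**Working it through.** **Nothing to reproduce.** The precision and detectable-effect figures are in Supplemental Tables 4 to 6, which are not shown. The check is therefore on the variance formula.

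**Inputs from the documents.** 150 centres (Design) and 4,924 patients (Inclusion and clinical follow-up), so 4,924/150 = 32.8 patients per centre on average; volume cut at 100; two-sided 0.05.

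**Assumptions not in the documents.**
- 5, 10 or 14 centres above 100 implants, holding 12%, 25% or 38% of patients
- 0.1 or 0.3 shock episodes per patient on average
- gamma patient frailty with variance 5
- gamma centre frailty with variance θ = 0, 0.05, 0.1 or 0.2. Since √0.05 = 0.22 and √0.2 = 0.45, the non-zero values mean that centre rates vary with a coefficient of variation of about 22% to 45%.

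**Method.** Poisson episodes with a constant baseline hazard, no true effect of the predictor, 1,500 runs per setting. With y episodes and t follow-up time, the rates are r_H = Σy/Σt in the high-volume class and r_L in the low-volume class, and b = log(r_H/r_L). Each patient contributes e = (y − r_H·t)/Y_H in the high class or −(y − r_L·t)/Y_L in the low class, where Y is the class total of episodes.
- Patient-clustered, as written: SE = √Σe²
- Centre-clustered: SE = √Σ_c(Σ_{i in c} e_i)²
- Type I error is the share of runs with |b/SE| > 1.96.

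**Result for volume (above against below 100).**

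| θ | true SD / patient-clustered SE | type I, patient-clustered | type I, centre-clustered, 10 or 14 high-volume centres | type I, centre-clustered, 5 high-volume centres |
|---|---|---|---|---|
| 0 | 0.98-1.00 | 0.04-0.06 | 0.065-0.075 | 0.11-0.13 |
| 0.05 | 1.15-1.29 | 0.09-0.13 | 0.07-0.09 | 0.12-0.14 |
| 0.1 | 1.29-1.51 | 0.13-0.21 | 0.07-0.09 | 0.13-0.14 |
| 0.2 | 1.43-1.83 | 0.16-0.28 | 0.06-0.09 | 0.14-0.16 |

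**Hand check of one setting.** Take 10 high-volume centres, 0.3 episodes per patient, θ = 0.1. With equal centre sizes within a class, the true variance is about SE² + θ(1/10 + 1/140) = 0.102² + 0.1 × 0.1071 = 0.0104 + 0.0107 = 0.0211. The SD is then 0.145 and the ratio 0.145/0.102 = 1.42. The simulation gave 1.47, with unequal sizes in the low-volume class.

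A ratio R implies a type I error of 2{1 − Φ(1.96/R)}. R = 1.15 gives 2{1 − Φ(1.70)} = 0.09 and R = 1.83 gives 2{1 − Φ(1.07)} = 0.28, which are the ends of the simulated range.

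**Result for a patient-level binary predictor** (0.3 episodes per patient, θ = 0.05 to 0.2), by the predictor's intraclass correlation (ICC) within centres:

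| ICC | type I, patient-clustered |
|---|---|
| 0 | 0.04-0.06 |
| 0.3 | 0.06-0.10 |
| 0.5 | 0.07-0.13 |
| 0.8 | 0.09-0.16 |

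Over these settings, and ICC 0.1, the centre-clustered error was 0.05-0.07.

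**The case against.** **The frailty may carry over.** The Andersen-Gill model extends the Cox model, the frailty sits under a general opening on multivariate analysis, and a condensed article may leave its combination with a robust variance to the full plan. This does not rescue the text. The shock paragraph names its own variance correction, at patient level, and its own fixed treatment of centre. If the fixed-effect sentence covers only the Wei, Lin and Weissfeld model, the shock model has no stated centre term at all.

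**The size is unknown.** This stands. The documents do not size the centre variance, and at zero the patient-level sandwich is correct. A reader might infer that the standard errors are too small in every case. The documents support only the conditional statement, though the plan's own premise makes the condition likely.

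**Few high-volume centres.** A reader might infer from the mean of 32.8 that only a handful of centres exceed 100. The article gives no centre sizes, and the arithmetic ceiling is 48 (4,924/101 = 48.8). The 5 to 14 used above is an assumption.

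**Volume and experience.** A reader might take the cut at 100 as the total over 2012-2019, so that early patients in a later large centre are labelled high-volume. No time window is stated. A count of prior implants would also answer a different question, the learning curve. Implant era is a listed predictor, and analyses stratified by calendar period and/or device generation are planned. This is a preference, not an error.

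**Limited reach.** This also stands. The cumulative incidences and mortality among the primary outcomes do not depend on this variance. Inference on predictors does.

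**Conclusion.** The point holds in conditional form. As written, the shock model tests a centre-level variable as if patients in the same centre were independent, which conflicts with the plan's reason for a random centre effect in the Cox model. This is a stated variance that does not fit the data structure, not a detail left out.

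Under the assumptions above, type I error is about 9-28% for volume and about 6-16% for a procedural predictor with ICC 0.3-0.8. It is nominal for predictors balanced across centres, or if centres do not differ beyond volume class. How far anaesthesia, incision technique or testing actually cluster by centre is not documented. The change should be made, but the descriptive results do not depend on it.

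**What to change.** 1. In the Andersen-Gill, negative binomial and Wei, Lin and Weissfeld models, cluster the robust variance by centre. Patients are nested in centres, so this also covers correlation within a patient.
2. Count the centres above 100 first. If there are few, add a few-cluster correction: with 5 such centres, plain centre clustering still gave 12-16% for θ = 0.05 to 0.2, and 11-13% even at θ = 0.
3. Alternatively, add the centre random effect already planned for the Cox model, but keep an allowance for recurrence within patients, for example a patient effect nested in centre. A centre frailty alone does not supply it.
4. Reconcile the two paragraphs: say which models the fixed volume effect applies to and whether the random centre effect stays beside it. State the time window for volume, and assign a centre with exactly 100 implants to a class.

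Replacing the volume class by the number of prior implants is optional.

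The cost is some added model specification and wider intervals for centre-level factors. No new data are needed, since the devices were listed by implanting centre.

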## Methods

### Design

The HONEST cohort is a French nationwide, single-arm, observational ongoing study that enrolled all patients who underwent implantation of an S-ICD (EMBLEM, Boston Scientific) between October 2012 (date of the first implantation in France) and December 2019 (Central Illustration). The study includes all 150 French Hospitals accredited to perform S-ICD implantations (Supplemental Table 1).

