## Preliminary results

Preliminary retrospective data from the HONEST cohort were presented during a Late-Breaking Science session at the 2022 European Society of Cardiology Congress. A separate focused analysis comparing patients with and without congenital heart disease was also published.^18^ Additional HONEST analyses have evaluated the long-term impact of defibrillation testing performed at the time of S-ICD implantation,^20^ as well as outcomes following S-ICD implantation after complications related to a prior transvenous ICD.^21^

Of the 4,924 patients included in the cohort, the majority were male (n = 3,776; 76.7%), with a mean age of 49.9 years.^22^ The indication for implantation was primary prevention in 3,119 patients (63.3%). Structural heart diseases are present in 3,851 patients (78.2%), with the most common etiologies being coronary artery disease (n = 2,026, 52.6%) and hypertrophic cardiomyopathy (n = 497, 12.9%). Among patients with electrical heart diseases, Brugada syndrome was the most frequently observed condition (n = 473, 44.5%). General anesthesia was used in 3,883 patients (78.9%), and intraoperative defibrillation was performed in 4,065 cases (82.6%).

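### The shock model clusters its variance on the patient and centre is cut to two volume classes; if centres differ within a class, intervals for centre-driven predictors are too narrow

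*Protocol article*

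**What the plan says.** All of this is in the protocol article, Statistical considerations.

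- **Second paragraph, Cox model.** "A frailty term will be included to account for variability between trial sites, with center effects embedded as random". The stated reason is that practice and experience differ from centre to centre.
- **Third paragraph, shocks.** An Andersen-Gill model, "incorporating a robust sandwich variance estimator to correct for correlations between recurrent events within the same subject".
- **Third paragraph, complications.** "the Wei, Lin and Weissfeld model will be employed to account for repeated events of different nature". No variance unit is written for this model.
- **Third paragraph, centre.** "The center effect will be examined as a fixed effect, categorized by centers with S-ICD implantation volumes greater or <100". This sentence directly follows the shock and complication models.

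The second paragraph also lists the prespecified predictors. Among them are implanting centre volume and these procedural choices: "incision technique [2-incision vs 3-incision], generator position [intermuscular vs subcutaneous], anesthesia type, defibrillation testing [performed vs not".

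On scale, the Design section states "The study includes all 150 French Hospitals accredited to perform S-ICD implantations", and Preliminary results gives 4,924 patients.

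**The concern.** A sandwich variance clustered on the patient allows a patient's own episodes to be correlated but treats different patients as independent. A two-class volume term removes only the average difference between large and small centres. Whatever differs among centres inside a class stays in the residuals and is shared by all patients of a centre.

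For a predictor that varies freely within centres this hardly matters. For one that varies mainly between centres, the reported standard error is too small. Centre volume is such a predictor by definition. Incision technique, generator position, anesthesia and defibrillation testing plausibly follow the habit of the centre.

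The Discussion names defibrillation testing and anesthesia among the questions the cohort should help to answer, and the plan calls p<0.05 significant without any alpha correction. An understated standard error therefore leads directly to technique or volume effects that are not there.

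**Working it through.** **No stated figure to reproduce.** The article gives no intraclass correlation (ICC), event count, centre-size distribution or standard error for these models. What follows fixes the direction from the documents and shows the size over assumed ranges.

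**1. Can two classes absorb the centre differences?** The mean is 4,924/150 = 32.8 patients per centre. Since 4,924/101 = 48.75, at most 48 centres can exceed 100 patients. At least 150 − 48 = 102 centres therefore share the low-volume class, and one binary term cannot describe differences among them.

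**2. Design effect for a predictor constant within centre.** DEFF = 1 + (m(1 + CV²) − 1) × ICC, with m = 32.8. The true SE is √DEFF times the reported one, and the coverage of a nominal 95% interval is 2Φ(1.96/√DEFF) − 1. Example with ICC 0.02 and equal sizes: 1 + 31.8 × 0.02 = 1.64, √1.64 = 1.28, coverage 87.5%.

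| Assumed ICC | DEFF, SE ratio, coverage (equal sizes) | DEFF, SE ratio, coverage (CV of size 1) |
|---|---|---|
| 0.005 | 1.16, 1.08, 93.1% | 1.32, 1.15, 91.2% |
| 0.01 | 1.32, 1.15, 91.2% | 1.65, 1.28, 87.3% |
| 0.02 | 1.64, 1.28, 87.5% | 2.29, 1.51, 80.4% |
| 0.05 | 2.59, 1.61, 77.7% | 4.23, 2.06, 65.9% |

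**3. Coverage by simulation.** There were 600 runs per setting with no true effect, using a Poisson rate model (Andersen-Gill with constant baseline) with the volume class included. Assumed: 4,924 patients in 150 unequal centres (CV of size 1.13, 6 centres above 100), 0.03 episodes per patient-year, follow-up of 3 to 7 years, and patient-level over-dispersion. At about 95% coverage the Monte Carlo error is √(0.95 × 0.05/600), or 0.9 points. Each cell gives coverage with the patient-level and then the centre-level sandwich.

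| Centre log-rate SD | Factor set by centre | Mostly centre-driven | Patient-level factor |
|---|---|---|---|
| 0 | 94.7%, 94.3% | 95.7%, 95.0% | 96.0%, 95.7% |
| 0.2 | 90.7%, 92.8% | 92.5%, 93.0% | 96.2%, 95.7% |
| 0.3 | 89.8%, 94.5% | 88.2%, 92.3% | 93.2%, 93.3% |
| 0.5 | 75.0%, 92.0% | 82.7%, 92.8% | 94.7%, 94.5% |

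The loss appears only where centres differ and only for centre-driven factors.

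**4. Rejection rates at nominal 5% by simulation.** A separate simulation with 600 runs per setting and CV of centre size about 1 also tested the volume term.

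| Centre log-rate SD | Technique, patient-level sandwich | Volume class, patient-level sandwich |
|---|---|---|
| 0 | 5.5% | 4.3% |
| 0.2 | 6.2% | 13.7% |
| 0.3 | 8.3% | 21.3% |
| 0.5 | 15.7% | 36.8% |

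With the sandwich clustered on centre, technique rejects 5.3 to 6.5%. Volume class still rejects about 9 to 14%; the contrast may rest on few large centres. A further simulation with about 1,100 episodes agrees for SD 0.3 to 0.5: 8 to 17% for technique and 19 to 38% for volume with the patient-level sandwich.

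**The case against.** The strongest reply is that the frailty may carry over. Andersen-Gill and Wei-Lin-Weissfeld are Cox-type models, the frailty is introduced under multivariable analysis in general, and the third paragraph does not withdraw it. The two-class term could then be an extra look at centre volume. This reading is possible but less natural: the third paragraph sets its own variance unit and calls centre a fixed effect directly after naming these models. Nor is the carry-over automatic. In a trial fit, R's coxph returned an error when a centre frailty and a patient-clustered sandwich were requested together. Even on this reading, the random and fixed specifications need to be reconciled in the text.

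Other parts of the reply stand:

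- **Complications.** A reader might infer that the plan fixes a patient-only variance for both models. It is written only for shocks. For Wei-Lin-Weissfeld it is implied by the usual method.
- **Size.** A reader might infer that false positives will run far above 5% in any case. The documents supply no input that shows this. With no centre variation there is no error. For a mostly centre-driven factor at SD 0.2, coverage is 92.5% against 93.0% with centre clustering, a difference within simulation error.
- **Reach.** A reader might infer that the primary results are compromised. Those are cumulative incidences from separate estimators, and the models in question address associated factors only.

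**Conclusion.** The point holds as a conditional one. If the third paragraph is followed as written, and centres differ within a volume class as the frailty in the second paragraph presumes, standard errors in the shock model are too small for predictors that vary mainly between centres. The same applies to the complication model if its usual patient-level variance is used.

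The size rests on assumed centre variation, centre sizes and event rates. For log-rate SD from 0 to 0.5 it runs from nothing to about 16% rejection at nominal 5% for a centre-preferred technique, and from nothing to about 37% for volume class. That technique follows centre habit is itself plausible but not documented; for volume it is true by definition. Patient-level predictors unrelated to centre keep their coverage (93.2 to 96.2% in the simulation). The documents do not support saying that all intervals are too narrow. The plan should be corrected on this point, but it leaves the primary cumulative incidence estimates untouched.

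**What to change.** Reconcile the second and third paragraphs of Statistical considerations. State that the sandwich variance of the Andersen-Gill and Wei-Lin-Weissfeld models is clustered on implanting centre, with volume kept as a covariate. Patients are nested in centres, so correlation within a patient stays covered. The negative binomial sensitivity analysis of shocks should follow the same rule.

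Treat the volume contrast separately, because plain centre clustering does not repair it. Use a centre random effect (with a patient random effect for recurrent events) or a small-sample-corrected cluster variance, and report how many centres fall in the upper class.

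The cost is a sentence or two in the plan, a small code change for the clustering and somewhat more work for the volume contrast. No new data are needed. Intervals for centre-driven factors will be wider if centres differ.

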**Figure 2 fig2:**
[figure not shown]
**Study Flowchart** The serial numbers corresponding to all S-ICD devices distributed in France from October 1, 2012, to December 31, 2019, were collected. Among 5,175 devices identified, 31 generators had been distributed to participating centers by the manufacturer but had not yet been implanted as of December 31, 2019, and 91 patients declined to participate. The final study population included 4,924 patients with de novo S-ICD implantation and 129 generator replacements, representing 98.2% of all patients implanted with an S-ICD in France during the study period. Abbreviation as in Figure 1.

Patient data, including baseline characteristics, procedural details, and follow-up events, were retrospectively collected in 2019/2020.^18^ A prospective follow-up phase began in 2020 and is planned to continue annually for 10 years.

A prespecified electronic case report form was used to collect the following data: demographic variables, indication for ICD therapy (primary vs secondary prevention), underlying heart disease (diagnosis and specific characteristics), left ventricular ejection fraction, procedural data (including anesthesia modalities, S-ICD generator model [EMBLEM model 1010, A209 or A219], use of defibrillation testing, need of an additional pacing system, among others), and follow-up data, including the use of remote monitoring (Latitude, Boston Scientific) and the occurrence and exact timing of clinical events. These events included device-related complications, appropriate or inappropriate therapies, reinterventions, heart transplantation, and death. Moreover, patients’ genetic findings, along with raw intracardiac electrograms data recorded during electric shocks, are systematically collected. A complete list of collected outcome events is provided in Supplemental Table 2.

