#### Study endpoints

The primary study outcomes at 5 and 10 years include 1) the cumulative incidence of appropriate shocks; 2) device-related complications, including inappropriate therapies, infection, lead dysfunction, and manufacturer-related recalls; 3) all-cause and cause-specific mortalities; and 4) requirement for pacing during follow-up.

An appropriate S-ICD shock was defined as any shock delivered for a ventricular arrhythmia with a ventricular rate exceeding the programmed therapy zone. Inappropriate shocks were defined as those triggered by nonventricular arrhythmias, T-wave oversensing, myocardial signals, or electromagnetic interference. Notably, shocks resulting from double counting of T-wave oversensing during slow ventricular tachycardia below the programmed therapy threshold was defined as inappropriate shock therapy. Surgical reintervention was defined as any procedure performed after initial implantation due to device-related complications. Local complications included premature battery depletion or pocket-related issues such as hematoma, localized or systemic infection, poor wound healing, and lead dislodgment. Early complications were defined as adverse events occurring within the first 30 days following S-ICD implantation. Late complications were defined as adverse events occurring beyond 30 days after S-ICD implantation.

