### Data management and study organization

Study data were centrally collected and managed using REDCap electronic data capture tools hosted at the Paris Cardiovascular Research Center (U 970, European Georges Pompidou Hospital, Paris, France). Specific REDCap modules were created for each work package to streamline data entry and review.

A steering and scientific committee oversaw study conduct, data quality, and progress (Supplemental Table 3). Participating sites entered S-ICD shocks and device- or procedure-related complications into a centralized database. In parallel, an independent external research assistant reviewed source documentation from electronic health records and S-ICD interrogations, including stored electrograms, to verify, harmonize, and standardize site-reported data across centers. A dedicated adjudication committee conducted centralized reviews of key clinical endpoints, including cause of death (with specific focus on SCD and S-ICD–related deaths), device infections, lead-related complications, and shock episodes. Electrograms were systematically retrieved via remote monitoring. Among all recorded shocks, electrograms were independently reviewed in a blinded manner by 2 expert electrophysiologists in 81% to classify shocks as appropriate or inappropriate and determine the underlying rhythm mechanism. Any discordance between adjudicators or between central adjudication and site assessment was resolved by discussion and final determination during annual consensus meetings. To minimize loss to follow-up, a systematic process was implemented across all 150 participating centers to ensure completeness of longitudinal data. Notably, the study collects all events, not just the first occurrence, for outcomes such as appropriate therapies, enabling a comprehensive assessment of event burden over time.^19^ Finally, vital status is comprehensively ascertained through systematic cross-referencing with the National Institute of Statistics and Economic Studies (INSEE, France) database.

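### The article's only censoring rule has no exception for all-cause mortality, so as written it stops a primary outcome at device removal or lost contact although national linkage supplies vital status

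*Protocol article*

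**What the plan says.** Under Study endpoints, the list that opens with "The primary study outcomes at 5 and 10 years include" has "all-cause and cause-specific mortalities" as its third item.

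Under Data management and study organization, the article reports that "vital status is comprehensively ascertained through systematic cross-referencing with the National Institute of Statistics and Economic Studies". It does not make this depend on the device being in place or on continued contact with a centre.

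Under Statistical considerations, the only censoring rule reads: "Follow-up will be censored in cases of loss to follow-up, device removal, death", and then the end of the study. It names no endpoint and makes no exception. The same section says: "For noncompeting events, Kaplan-Meier curves will be used". Nothing competes with death from any cause, so all-cause mortality falls under that sentence.

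**The concern.** For shocks and device complications, ending follow-up when the device comes out is natural, because the patient can no longer have the event. Death is different. A patient whose device has been removed can still die, and the national linkage can still find that death.

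Kaplan-Meier treats a censored patient as having the same future risk as those who remain under observation. That is doubtful here. The article collects events that may accompany removal and may bear on prognosis: "These events included device-related complications, appropriate or inappropriate therapies, reinterventions, heart transplantation, and death". It also makes "requirement for pacing during follow-up" a primary outcome, and a pacing need is a possible reason to change system. If removal or lost contact goes with a different risk of death, the mortality curve describes survival while the device is in place and under observation, not survival of S-ICD recipients from implant.

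The article presents the cohort as independent postmarket surveillance and has a committee look specifically at S-ICD-related deaths. A death after explant for infection is one that such a study would want to keep, and the rule as written leaves it out.

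**Working it through.** **Reading the passages together.** Mortality is primary; its source is independent of device and site; the only censoring rule stops at device removal and at loss to follow-up; no separate rule for mortality appears in the article. Taken literally, deaths after either event are not counted.

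**No figure to reproduce.** The article gives no mortality rate, removal rate, loss rate or expected number of deaths. What follows is an illustration on assumed rates.

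**Inputs**
- From the article: N = 4,924; horizons T = 5 and 10 years.
- Assumed: death hazard with the device m = 0.03 or 0.05 per year; removal (or loss) hazard r = 0.01 or 0.02 per year; death hazard afterwards h × m, with h = 0.5, 1, 2 or 3. All hazards are constant.

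**Formulas**
- Alive with device: P0 = exp(−(m + r)T).
- Alive after removal: P1 = r[exp(−hmT) − P0] / (m + r − hm).
- True cumulative mortality = 1 − P0 − P1.
- Kaplan-Meier limit when censoring at removal = 1 − exp(−mT).
- Deaths counted under the rule = N × m/(m + r) × (1 − P0).

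**Smallest understatement at 10 years** (m = 0.03, r = 0.01, h = 2)
- P0 = exp(−0.4) = 0.6703.
- P1 = 0.01 × (0.5488 − 0.6703)/(−0.02) = 0.0608.
- True mortality 26.9%; under the rule 1 − exp(−0.3) = 25.9%; gap 1.0 point.

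**Largest understatement at 10 years** (m = 0.05, r = 0.02, h = 3)
- P0 = exp(−0.7) = 0.4966.
- P1 = 0.02 × (0.2231 − 0.4966)/(−0.08) = 0.0684.
- True mortality 43.5%; under the rule 1 − exp(−0.5) = 39.3%; gap 4.2 points.

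**All combinations of m and r: estimate under the rule minus truth, in percentage points**

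| Hazard after removal | 5 years | 10 years |
|---|---|---|
| halved (h = 0.5) | +0.2 to +0.5 | +0.6 to +1.6 |
| equal (h = 1) | 0 | 0 |
| 2-3 times higher | −0.3 to −1.6 | −1.0 to −4.2 |

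**Equal hazards: information lost.** With m = 0.03 and r = 0.01 at 10 years, the rule counts 0.75 × (1 − 0.6703) = 24.7% against 25.9% in truth, so about 59 deaths in 4,924 patients go uncounted. With m = 0.05 and r = 0.02 the number is about 167.

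**Yardstick.** A simple binomial 95% half-width, 1.96 × √[p(1 − p)/4,924], is about 1.0-1.2 points at 5 years and 1.2-1.4 points at 10 years. The smaller gaps lie inside it and the larger ones exceed it.

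**The case against.** The strongest reply concerns scope. The rule lists death as a reason for censoring, which cannot literally apply when death is the event. It also comes directly after the paragraph on recurrent-shock and complication models. It was probably written for device outcomes, and a fuller protocol or analysis plan may treat mortality separately. This bears on intent and lowers the severity, but it does not remove the point. The sentence stands among general statements on proportional hazards and missing data, no other censoring rule is given, and one that is unsuitable for a primary outcome has been stated, not merely left out.

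A second reply is that someone whose vital status is in a national database is hardly lost for all-cause mortality, so that part of the rule may seldom apply. That is fair; device removal is the firmer half.

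A reader might go further and infer that known deaths are being lost selectively and that S-ICD mortality will therefore look too favourable. The documents do not support that. They give no removal rate, mortality rate or post-removal hazard; removal might also occur in lower-risk patients; and the same model gives no bias at equal hazards and an overstatement at a halved hazard. The annual mortality of 3-5% is itself an assumption, for a cohort with a mean age of 49.9 years.

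A reader might also worry about the opposite error, in which linked deaths are counted while living drop-outs are cut at last contact. No passage describes that practice. Nor does the article say that the linkage supplies cause of death, which is settled by committee review. The argument is thus firmest for all-cause mortality.

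**Conclusion.** The point holds as a defect in the stated rule: with no exception for mortality, it censors a primary outcome at events that need not end the observation of death. The estimate is biased whenever mortality after removal or loss differs from mortality with the device in place. Neither direction nor size can be fixed from the documents. Over the assumed rates the 10-year error runs from about 4.2 points too low to 1.6 points too high, and the 5-year error from about 1.6 too low to 0.5 too high. At equal hazards the only cost is precision. Comprehensive ascertainment is the article's own description; it gives no completeness figure for the linkage. Because the intent was probably narrower than the wording, and the cohort is single-arm and descriptive, this is a should-fix.

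**What to change.** Make censoring specific to the endpoint:

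- **All-cause mortality:** follow every patient from implant to death or the date of the vital-status linkage, whatever happens to the device or to site contact.
- **Cause-specific mortality:** use the same follow-up, and keep deaths whose cause cannot be adjudicated in a separate cause-unknown category, because the linkage is not said to supply cause.
- **Shocks and device complications:** keep censoring at device removal.
- **On-device mortality:** if an estimate that stops at removal is wanted, label it as secondary.

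The cost is a short addition to the statistical section. For all-cause mortality no new data are needed, since the linkage already exists. The reported mortality may change slightly, in a direction that cannot be told in advance.
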